### Research aims

This study involves an effect evaluation (RCT) and a process evaluation (qualitative research) of SEd. The first question that will be addressed is:
A)What is the effect of the SEd intervention on remaining at school (primary outcome), study success and student satisfaction (secondary outcomes) of students with mental health problems who follow post-secondary education, as compared to students with mental health problems who receive support as usual plus advice from a trained educational staff member on potential supportive resources?

We plan to test the following hypotheses:
More students who receive the SEd intervention will remain at school or graduate as compared to students who receive support as usual plus advice on potential supportive resources.Students who receive the SEd intervention will be more successful at school, operationalized as a higher GPA and a higher number of credits and courses completed, than students who receive support as usual plus advice on potential supportive resources.Students who receive the SEd intervention will experience a higher level of satisfaction at school than students who receive support as usual plus advice on potential supportive resources.

The second research question that will be addressed is:
B)What are the essential components of the SEd intervention according to students and SEd specialists?

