### Participants

Study participants are students with mental health problems who want to complete their current education studying at Mbo Utrecht, which is an educational institute that provides post-secondary vocational education, or at the Hanze University of Applied Sciences Groningen, an educational institute for higher professional education. They will be recruited through personal contact with educational professionals, information brochures (see Additional file 1), posts on the internal website of the schools, posters and social media. Inclusion criteria are:
having a mental health condition (e.g. depression, anxiety disorder, bipolar disorder, psychosis, ADHD) for which the student has received a formal diagnosis or the student experiences symptoms for at least 6 months, and;receiving treatment for mental health problems or having received treatment in the past, and;being at least 16 years of age, and;following regular post-secondary vocational education in Utrecht; or higher education in Groningen, and;expressing the need for extra support to remain at school.

Exclusion criteria are:
not fluently speaking and reading in Dutch, or;the need for extra support is only expressed by others than the student, or;unable to give informed consent, or;less than six months to go before graduation, or;has received SEd services in the past

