### Study procedures

We adhere to the SPIRIT 2013 guidelines [40], the checklist is provided in the Additional file 2.

Students who heard about the study through one of the recruitment strategies and are interested in participation, contact the research team by e-mail. A data coordinator will check the inclusion criteria and will then send a link to an online questionnaire which starts with information about the study and the question to fill out an informed consent form. In the informed consent (see Additional file 3), students state that they have been informed about the study and that they participate voluntarily. In addition, they give permission to collect grades and course credits from the school’s administration for the next five years, so we are able to follow the study success of the students after the current project has finished. They also give permission that in case they drop-out of the study, school progress keeps being monitored. Students have the right to withdraw this permission at any moment in time.

After signing the informed consent, the students fill out the baseline-questionnaire. Then, students will receive a student ID number and will be randomized, for both educational institutes separately, by the data coordinator in either the experimental condition (Supported Education-coaching; half of the group of students) or the control condition (support as usual plus advice on potential resources; half of the group of students), using the minimization approach [41] which aims to minimize imbalance between the conditions on specific factors, in our case on gender, age, ethnicity, study year, level of study, the number of credits completed, and level of psychological distress. The condition to which the student is allocated depends on the characteristics of the students that were already enrolled. Students will receive compensation (a gift coupon of 12,50 euro each) for filling in the questionnaires at baseline, 6- and 12-month follow-up. Within this 12-month follow up, each student experiences a critical moment in the educational pipeline: either transitioning to the next year or graduating. In Table 1, the Spirit flow diagram of the study procedure is presented.

**Table 1 Tab1:** SPIRIT flow diagram of the study procedure showing enrolment, interventions, and assessments

	Pre-intervention	Post-intervention (within one month)	6 month follow-up	12 month follow-up
**TIMEPOINT**	**t**_**0**_		***t***_***1***_	***t***_***2***_

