#### Secondary study outcomes

Secondary study outcomes are study success and student satisfaction.

*Study success* will be measured with the following indicators: grade point average per semester; number of credits completed per semester; and number of courses completed.

*Student satisfaction* will be determined by the school subscale of the Multidimensional students’ life satisfaction scale [48, 49], which consists of eight items measuring the overall satisfaction of the student at school. Students indicate on a 4-point scale, ranging from 1 (Rarely) to 4 (Always) to what extent the statements, such as ‘I like the activities at school’ and ‘I learn a lot at school’ are applicable to them.

Furthermore, the following measures will be included in order to examine whether the scores of the students in the two conditions differ on these aspects which could account for any possible effects:

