### Proposed analyses

Analyses will be performed according to the intention-to-treat principle and we will control for any variation in observable characteristics between conditions that remained after the minimization procedure that was used to randomize the students into the conditions. Missing values in the questionnaires will be prevented as the questionnaires are administered through an online secure software program (Enalyzer) in which answering to all items is obligated. The main outcome measure (remaining at school) will be insensitive for missing values as this data can be retrieved from the administration offices of the educational institutes. In case of missing data (for example, when a student does not fill in the second or third questionnaire), intention-to-treat analyses will be performed to account for incomplete outcome data [55]. In addition, it will be examined whether the rates of incomplete data differ between the control and experimental condition. To detect any outliers, the median absolute deviation method will be used [56]. Unrealistic outliers (due to e.g. data entry mistake) will be removed. In case of outliers with a realistic value, we will perform the analyses both with and without the outliers and we will report both results.

Descriptive statistics (e.g. frequencies, means and standard deviations) will be provided for all variables. Conventional statistical tests (e.g. regression, chi-square and ANOVA) will be used to address the research questions in accordance with how the data align with the assumptions of these tests (e.g. normality, homogeneity). In case the data are not normally distributed, the non-parametric equivalents will be used (e.g. the Friedman-test, the Mann-Whitney-test and the Wilcoxon signed-rank test).

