With respect to the primary outcome, remaining at school, we will compare the number of students who remained in education or graduated in the experimental and the control condition at T2. Logistic regression models will be conducted to test the differences between the experimental and control condition. In addition, the differences in scores on the secondary outcomes, study success and student satisfaction, will be examined for T0 to T2 using chi squares or repeated measures of variance with the ANOVA test using 95% confidence levels, respectively. Furthermore, the differences between the two conditions on number and duration of contacts with the SEd specialist, the trained staff member or students service provider; the number of study skills where the students need support with and the number of resources needed or used when studying, student general self-efficacy levels and the working alliance with the professional, will be calculated using the ANOVA test with 95% confidence levels. Moreover, to test whether outcomes are similar for students from both educational institutions, sensitivity analyses will be performed excluding students from the institute for intermediate vocational education.

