A bottleneck of many RCTs is the low influx of participants [62–64]. Therefore, in this study we will be attentive on the inclusion speed: can a sufficient influx of students be expected per site; is there still a willingness to participate at the various levels of the organization, and are disturbing factors for the project expected (e.g. a reorganization)? In addition, we will closely monitor the influx of students during the recruitment phase by evaluating monthly if recruitment rates are on track, in order to identify potential problems in time and initiate additional actions to boost inclusion.

In order to recruit a sufficient number of students, we asked the advisory board to advise us about relevant recruitment strategies. The recruitment strategies that were mentioned like posts on the internal website of the schools and on social media, posters, information brochures and personal contact with educational professionals will be used in the study.

To increase the chance that we reach a sufficient number of students for our study, we decided that the inclusion period of students is six months. Consequently, there will be differences at baseline being the point in the school year the student is enrolled in the study. However, we expect these differences to be the same in the experimental and control condition. We will report this information and if necessary, we will take it into account during the data analysis.

In addition, the attrition of participants can be a threat to studies in which follow-up measurements are used [63, 65]. In the informed consent form of our study, students give permission to collect information about their school progress (drop-out, grades, and course credits) from the school’s administration system also in case they drop-out of the study. In this way, complete and objective data regarding our primary outcome (remaining in school) and a part of our secondary outcomes (study success) are guaranteed.

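### Access to school records cannot guarantee complete study-success data: semester GPA stops when a student leaves school or graduates, so the T0–T2 GPA comparison is made in a group selected partly by the primary outcome

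*Protocol article*

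**What the plan says.** The Discussion of the protocol article treats attrition as a threat to follow-up. Its answer is that students permit retrieval of school-progress data even if they drop out of the study, so that "complete and objective data regarding our primary outcome (remaining in school) and a part of our secondary outcomes (study success) are guaranteed".

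Study success is defined under Secondary study outcomes as "grade point average per semester; number of credits completed per semester; and number of courses completed". The second hypothesis under Research aims predicts better study success with SEd, "operationalized as a higher GPA and a higher number of credits and courses completed". Under Proposed analyses, differences in the secondary outcomes "will be examined for T0 to T2 using chi squares or repeated measures of variance with the ANOVA test". For missing data, such as a skipped follow-up questionnaire, the same section says that "intention-to-treat analyses will be performed to account for incomplete outcome data".

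Two other statements bear on the point. The Participants section excludes only students with "less than six months to go before graduation", so some participants can graduate before the 12-month assessment. Study procedures adds, about the consent to use school data: "Students have the right to withdraw this permission at any moment in time".

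**The concern.** The completeness statement answers one kind of drop-out and overlooks another. A student who drops out of the study but stays enrolled still generates grades, and the school can supply them. A student who drops out of school generates none, and no permission can retrieve a GPA for a semester that was not followed.

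Leaving school is the primary outcome. GPA is therefore absent for the students who fail on that outcome, and their number is expected to differ between arms if SEd works. The remaining comparison is between groups selected after randomisation. If SEd keeps some academically weaker students enrolled, they enter the SEd average while their counterparts are absent from the control average. Success on the first hypothesis would then pull down the GPA part of the second.

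Graduates before T2 have the same gap for a different reason: they count as successes on the primary outcome but have no later semester.

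**Working it through.** **1. Which outcomes exist after a student leaves school?**

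| Outcome | After leaving school | After graduating before T2 |
|---|---|---|
| Enrolment status | defined | defined (counts as success) |
| Credits, courses completed | defined (no more earned) | defined up to graduation |
| GPA for semesters already followed | defined | defined |
| GPA for later semesters | does not exist | does not exist |

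Only the last row contradicts the completeness statement. School satisfaction is outside that statement. Separately, its scale is described as "eight items measuring the overall satisfaction of the student at school", and such items no longer apply to someone who has left.

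**2. Does the stated analysis handle it?** Whether the test used is a chi-square or a repeated-measures ANOVA, a student needs a T2 GPA to contribute to a T0–T2 comparison. Intention to treat keeps students in their randomised arm. It does not say what value stands for a grade that does not exist.

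**3. How large could the bias be?** The protocol has no figure to reproduce here, so a simple selection model serves.

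- Let GPA be standard normal in both arms, with no effect of SEd on anyone's grades.
- Let a student remain enrolled when a latent retention score, correlated rho with GPA, exceeds a cut-off c that gives retention p.
- Mean GPA among those remaining = rho × φ(c)/p.
- Bias (SEd minus control) = rho × [φ(c_SEd)/p_SEd − φ(c_control)/p_control], in SD units.

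Retention and rho are assumptions. The only drop-out figure in the document is about 15% after five years, from a cited study (Background). At a constant annual rate this gives 0.85^(1/5) = 0.968, or about 97% retention at one year. Students who ask for support to stay at school may leave more often, so lower rates are shown too.

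Values of φ(c)/p:

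| p | φ(c)/p |
|---|---|
| 0.99 | 0.027 |
| 0.97 | 0.070 |
| 0.92 | 0.162 |
| 0.85 | 0.274 |
| 0.70 | 0.497 |

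Bias in SD units (differences taken before rounding):

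| Retention, control vs SEd | Difference in φ(c)/p | rho = 0 | rho = 0.3 | rho = 0.5 | rho = 0.7 |
|---|---|---|---|---|---|
| 97% vs 99% | -0.043 | 0 | -0.01 | -0.02 | -0.03 |
| 85% vs 92% | -0.113 | 0 | -0.03 | -0.06 | -0.08 |
| 70% vs 85% | -0.222 | 0 | -0.07 | -0.11 | -0.16 |

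With rho = -0.3 (better students leave) the sign reverses: +0.01, +0.03 and +0.07.

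**4. Against sampling error.** With 70 per arm and 85% vs 92% retention, 59.5 and 64.4 students would be expected to have a final GPA. The standard error of the difference is about √(1/59.5 + 1/64.4) = 0.18 SD. With 70% vs 85% (49 and 59.5 students) it is √(1/49 + 1/59.5) = 0.19 SD.

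**The case against.** The strongest defence is that the sentence sits in a paragraph about attrition from the study, and for that purpose it is largely right. A condensed article may also leave the derivation of GPA for leavers to a fuller document. Both points have weight. But the sentence is an affirmative statement that study-success data will be complete, and study success is defined to include GPA per semester. It is wrong for that indicator, whatever another document may add.

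Several stronger readings are tempting and not supported:

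- A reader might infer that a retention benefit must make SEd look worse on grades. It need not. The bias requires both a retention difference and poorer grades among the students SEd retains. The Background mentions students dismissed on academic grounds, but also leavers in good academic standing. At zero correlation there is no bias.
- A reader might infer that the whole second hypothesis is undermined. Credits and courses stay defined for leavers, and better retention should raise them. Only GPA is affected.
- A reader might take satisfaction to be part of the guarantee. The sentence covers only study success among the secondary outcomes, and Proposed analyses openly allows for missing questionnaires.
- A reader might convert the planned effect size of 0.5 into a specific retention difference and quote a bias from it. The protocol does not state the scale of that effect size, so no planned pair of retention rates can be derived from it.
- A reader might fear that the outlier rule would delete zero credits for leavers. Only unrealistic values are removed. Realistic outliers are analysed both with and without.

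It also stands that every bias shown is below one standard error of the GPA difference.

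**Conclusion.** The point holds, limited to GPA. The completeness statement is wrong for semester GPA after school drop-out or graduation, and the T0–T2 GPA comparison, followed as written, is not a comparison of all randomised students. The possibility of withdrawing permission further weakens the word guaranteed, for every record-based outcome.

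The direction is probably against SEd, on the condition that it retains weaker students. The size is modest: from zero to -0.16 SD over the range examined, and no more than -0.03 SD if one-year drop-out is as low as the cited five-year figure suggests. These values rest on assumed retention rates, an assumed retention–grade correlation and a normal selection model. The primary outcome is not affected by this gap.

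A correction is worthwhile because the statement is factually wrong for a named outcome and the remedy is cheap.

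**What to change.** 1. Limit the completeness statement in the Discussion to enrolment status, credits and courses completed, and make it subject to withdrawal of permission.
2. Analyse credits and courses in all randomised students. Count zero for semesters after school drop-out. For graduates, express the result relative to the credits scheduled up to graduation.
3. Report T2 GPA as conditional on still being enrolled, with the number contributing in each arm.
4. Add one all-randomised sensitivity analysis of GPA that ranks school drop-outs lowest and represents graduates by their last available GPA.
5. Note that the school-satisfaction items do not apply to students who have left school, as a separate remark and not as part of the completeness statement.

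Making credits the leading study-success indicator would be a preference and is not needed to correct the error.

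The cost is some wording and a little more analysis from records already collected. The small downside is that T2 GPA carries less weight as a randomised comparison.

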## Data Availability

Not applicable.

## Abbreviations

ADHD: Attention Deficit Hyperactivity Disorder
GPA: Grade Point Average
Hbo: Higher professional education (in Dutch: Hoger beroepsonderwijs)
Mbo: Intermediate post-secondary vocational education (in Dutch: Middelbaar beroepsonderwijs)
PR: Psychiatric Rehabilitation
PRA: Psychiatric Rehabilitation Approach
RCT: Randomized Controlled Trial
SCL-10: Symptom Checklist-10
SEd: Supported Education
SPIRIT: Standard Protocol Items: Recommendations for Interventional Trials
WBP: Personal Data Protection Act (in Dutch: Wet Bescherming Persoonsgegevens)
